#### Planned Analyses

The primary aim of this study is to determine the feasibility, acceptability, and preliminary efficacy of the tailored PA intervention. We will consider the intervention feasible if at least 80% of the randomized participants are retained at the 6-month follow-up. The intervention will be considered acceptable if at least 80% of participants completing the 6-month follow-up respond favorably (*satisfied* or *very satisfied*) to the question *In general how satisfied were you with the intervention?* on the 6-month follow-up survey. We also asked more questions about intervention and study acceptability on the 6-month survey and the poststudy qualitative interviews described earlier. The main efficacy outcome was minutes per week of total MVPA, as measured by accelerometer data and PAR self-report, assessed at baseline and 6 months after baseline. The hypothesis is that participants in the PA intervention condition will have greater increases in minutes of total MVPA from baseline to post intervention (6 months) than participants in the control condition.

As a preliminary step, we will assess potential between-group differences in baseline characteristics (demographics and baseline PA level) using graphical methods and nonparametric and parametric tests as appropriate (eg, the Wilcoxon rank sum test for skewed data, *t* tests for normally distributed continuous data, and chi-square tests for categorical data). Any variables not balanced by randomization will be controlled for as covariates in subsequent analyses if they are correlated with the outcome (eg, minutes per week of MVPA) at a modest *P*<.10 level. We will estimate the preliminary efficacy of intervention compared with control using a generalized linear model in which we regress minutes per week of objectively measured MVPA at 6 months on the treatment assigned, baseline value of the outcome, and potential confounders (including those variables not balanced by randomization). To avoid the effects of outliers, we apply a normalizing transformation (if necessary) to the outcome before analysis. Should this transformation not adequately bring the data toward normality, we will model the median outcome (instead of the mean) using a quantile regression model.

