Modeling is performed using a likelihood or quasi-likelihood–based approach and, thus, makes use of all available data (intent-to-treat sample) to produce consistent estimates of the regression parameters. Our goal is to estimate effect sizes, rather than strict statistical hypothesis tests. A similar modeling strategy will be used to estimate effects on self-reported minutes per week of MVPA.

Potential moderators will be examined using a similar analytic approach to that described earlier. For example, the total PA at 6-month follow-up (as measured by the accelerometer) will be regressed simultaneously on each moderator (eg, neighborhood PA environment profiles), as determined by latent class analysis, treatment assignment, and the interaction between the 2. If the interaction term is nonzero, we will conclude that there is evidence for a potential moderator. Models will also control for potential confounders of the association, including baseline PA and any variables unbalanced between arms. Our interest is in estimating effect sizes for conditional effects rather than strict statistical hypothesis testing.

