Although the intervention focuses mostly on changing the psychological, behavioral, and economic barriers to PA, we will explore potential moderating effects of individual and environmental factors on PA. At the individual level, we will examine whether important demographics (eg, age, country of origin, marital status, and education), acculturation, or baseline stage of change (based on TTM) impact changes in PA among Latino men. At the neighborhood level, we will explore walkability and social conditions, which have not been reported in PA intervention studies with Latino men. Although many studies explore associations of neighborhood walkability with PA (including studies with Latinos) or as a potential moderator of intervention efficacy [100-104], associations between other neighborhood social conditions and PA remain unanswered. This study will provide preliminary evidence for some of these unanswered questions. For example, this intervention will examine whether perceived neighborhood-based police profiling impacts PA among Latino men. In previous qualitative studies with disparity groups, neighborhood race and gender-based police profiling is cited as a potential barrier to PA for racial or ethnic minority men [89,105]. Consequently, this study seeks to build upon the limited available evidence for Latino men by exploring the potential moderating effects of these individual and environmental variables in a PA-focused pilot RCT.

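### The rule for concluding moderation, a nonzero interaction term, has no threshold and would label essentially every candidate a potential moderator

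*Protocol article*

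**What the plan says.** The protocol article (Overall Design) lists potential moderators, together with potential mediators, as secondary aims. Under Planned Analyses, "Potential moderators will be examined using a similar analytic approach to that described earlier": accelerometer-measured activity at 6 months is regressed on the moderator, treatment and their interaction, with control for baseline activity and unbalanced variables. The conclusion is then fixed by one sentence: "If the interaction term is nonzero, we will conclude that there is evidence for a potential moderator". The paragraph ends: "Our interest is in estimating effect sizes for conditional effects rather than strict statistical hypothesis testing".

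The main model is a generalized linear model for minutes per week, transformed if necessary. If transformation fails, "we will model the median outcome (instead of the mean) using a quantile regression model".

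The Discussion (Importance of the Study) names the candidates. At the individual level, "we will examine whether important demographics (eg, age, country of origin, marital status, and education), acculturation, or baseline stage of change" affects change in activity. At the neighborhood level, "we will explore walkability and social conditions, which have not been reported in PA intervention studies with Latino men". It adds that "this intervention will examine whether perceived neighborhood-based police profiling impacts PA among Latino men".

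**The concern.** The sentence is a decision rule: it says what will be concluded and when. A rule of that kind has to be able to come out either way. This one, read literally, almost never can, because a regression coefficient estimated from data is practically never exactly zero. A finding of evidence would then say nothing about whether the intervention works differently in different men.

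The rule also conflicts with its own paragraph. If the aim is to estimate effect sizes, no yes/no conclusion should hang on the estimate. If a conclusion is to be drawn, some criterion is needed, and the disclaimer of testing takes away the most natural one.

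At stake is the report on one secondary aim. Readers could be told that a long list of demographic, acculturation and neighborhood variables are potential moderators when the data cannot separate them from noise.

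**Working it through.** **Inputs from the protocol article.** 25 men per arm planned, two-sided α .05, d=0.51, and mean changes of 42.5 (SD 81.8) versus 9.0 (SD 45.7) min per week (Power Analysis); 43 randomized (Results); 80% retention benchmark (Planned Analyses), and 0.80 × 43 = 34.4, taken as 34.

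**Assumptions not in the article.** A binary moderator split 50/50, four equal moderator-by-arm cells, normal errors, and independent candidates where several are counted together.

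**1. The plan's own figures reproduce.** The pooled SD is √((81.8² + 45.7²)/2) = 66.3, so d = 33.5/66.3 = 0.51. With 25 per arm, power at d=0.51 is 43.8% (normal) or 42.4% (t), against 43% stated. At d=0.75 it is 75.5% or 73.8%, against 75%. The moderator rule has no stated figure to reproduce.

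**2. Count of candidates.** Age, country of origin, marital status, education, acculturation and stage of change make 6. Walkability and social conditions make 8. Police profiling, counted separately, makes 9. The demographics are given as examples, so the true number may be higher.

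**3. The rule with no true moderation.** A simulation used a baseline-adjusted linear model with a treatment-by-moderator product and a true interaction of zero, with 20,000 fits at each sample size.

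| N | Estimate nonzero | 95% CI excludes zero |
|---|---|---|
| 50 | 100% | 5.0% |
| 43 | 100% | 4.9% |

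The first column needs no simulation: it follows from the estimate being effectively continuous and does not depend on the 50/50 split.

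**4. How large chance estimates are.** With four equal cells the interaction variance is 16σ²/N, so SE = 4/√N in SD units. With no true moderation, the expected absolute estimate is SE × √(2/π) = 0.798 × SE.

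| N | SE | Expected absolute estimate | 95% CI half-width (1.96 × SE) |
|---|---|---|---|
| 43 | 0.61 | 0.49 | 1.20 |
| 34 | 0.69 | 0.55 | 1.34 |

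At N=43 an absolute estimate above 0.51 SD arises by chance about 40% of the time. Power to detect a true interaction of 0.51 SD is about 13%.

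**5. If a CI criterion were used to name moderators.** Over nine independent candidates, the chance of at least one false label is 1 − 0.95⁹ = 0.37. At N=43 only estimates beyond about 1.20 SD would qualify, more than twice the planning main effect (1.20/0.51 = 2.4), so a named moderator's effect would probably be exaggerated.

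**The case against.** The best defense is that nonzero refers to the parameter and is shorthand for an interval that excludes zero, with the criterion left to a statistical analysis plan. The label is only a potential moderator, the Discussion frames the work as exploratory and preliminary, and the paragraph puts estimation ahead of testing.

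Part of this stands. The analysis is exploratory, the wording is cautious, and no primary outcome, sample size or progression criterion depends on it. The reading as shorthand has no support in the text: no criterion is given, and the neighboring sentence steps away from testing. Nor is this a detail simply left to another document, since the article itself states the rule.

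Some stronger readings are tempting, but the article does not support them:

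- *A reader might infer that every candidate must be declared a moderator.* That is too strong, because the median-regression fallback can return exactly zero, for example if many men have no bouted activity.
- *A reader might infer that the latent classes are unstable and their uncertainty ignored.* The article gives classes only as an example ("neighborhood PA environment profiles), as determined by latent class analysis"). It does not give the number of indicators, their coding, the number of classes, the sample used for fitting, or how class membership is carried into the model. Those details may sit elsewhere.
- *A reader might infer that the labels will steer targeting in the next trial.* No section says so. The larger trial is tied to feasibility, acceptability and preliminary efficacy, and its sample size to the between-group effect.

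**Conclusion.** The concern holds for the rule as worded. In the mean model, the condition for concluding evidence is met practically always, so the conclusion carries no information, and it contradicts the estimation aim stated in the same paragraph. That result needs no assumption about the moderator's distribution.

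The size of chance estimates, 0.49 to 0.55 SD on average for 43 to 34 men, does rest on a 50/50 binary moderator with equal cells; an uneven split would make it larger. It shows that a visibly large interaction would not be informative by itself in this trial.

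The matter is worth correcting but limited in reach: it bears on one of two exploratory secondary aims in a pilot and leaves the primary conclusions untouched.

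**What to change.** Delete the sentence with the nonzero rule. Replace it with wording such as: *Each treatment-by-moderator interaction will be reported with its 95% CI as hypothesis-generating. The number of moderators examined will be stated. Where the CI includes zero, the data will be described as inconclusive about moderation.*

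If the investigators still wish to name a potential moderator because its interval excludes zero, the report should add two cautions: with about nine independent candidates at 5% each, the chance of at least one false label is about 37%, and the estimate for a variable selected in this way is likely exaggerated.

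The cost is a few sentences of wording. No model, moderator or data item changes. Follow-up data collection ended in April 2020 while analysis was ongoing, so the change should be recorded as made after data collection. The real downside is that few or no moderators will be named, which is what a trial of this size can support.

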## Results

This study was funded in September 2016. Initial institutional review board approval was received in February 2017. Focus groups and intervention development were conducted from April 2017 to January 2017. Recruitment for the clinical trial was carried out from February 2018 to July 2019. Baseline data collection was carried out from February 2018 to October 2019, with a total of 43 participants randomized. Follow-up data were collected through April 2020. Data cleaning and analysis are ongoing, and we expect study results to be published in summer 2021.

## Discussion

### Importance of the Study

PA is a critical health behavior known to promote health and prevent the onset of chronic diseases and mortality [1,96,97]. Previous research indicates that Latino men are underserved with respect to inclusion in interventions designed to increase PA [16-18]. Therefore, this study addresses these research gaps by specifically targeting diverse subgroups of underserved Latino men (ie, Caribbean and Central and South American) and engaging them in the intervention design [10,98]. This engagement is critical as (1) the majority of PA research with Latino men to date has involved mainly Mexican Americans [21,55], and these results may not generalize to other Latino men subgroups, and (2) there may be additional cultural considerations for retention of non-Mexican Latino men and their perceived acceptability of a PA intervention [10,18,98]. As such interventions remain untested with diverse Latino men, we designed this novel tailored web- and text-based PA intervention and piloted it in a feasibility RCT with these diverse groups of Latino men. If the results of the pilot study provide support for feasibility, acceptability, and preliminary efficacy, then a larger, fully powered efficacy RCT will be tested with diverse Latino men.

The Hombres Saludables study leverages theories of behavior change and low-cost, technology-based intervention delivery mechanisms that demonstrate high reach with Latinos, most of whom use the internet and own a cell phone [29,30], although future research should consider that internet usage for health-related purposes may vary by the Latino subgroup [98]. These theoretical and technological components have demonstrated efficacy in other populations [32-34], including Latinas [11-15,37]. For Latino men, however, studies documenting the efficacy and effectiveness of such low-cost interventions are lacking [16-18]. In the limited intervention research that does exist, 98% of the 48 participants in one study identified as either Mexican or Mexican American. The intervention focused on weight loss, not specifically PA, and involved weekly in-person individual sessions with a bilingual, bicultural Hispanic male lifestyle coach, which, although effective in increasing leisure time PA, raises cost, replicability, and scalability concerns [21]. Another small study with 45 Latino participants (mostly Mexican American) delivered a 6-month intervention wherein participants received a baseline counseling session and then individually tailored PA print materials and text messages. Intervention participants increased their total MVPA significantly more than the control group [22]. Thus, the findings from the Hombres Saludables study will contribute to intervention research by providing preliminary evidence of how integration of theories of health behavior change with internet and text-based intervention components may impact PA among diverse Latino men, a disparity group with low levels of leisure time PA [2,10].

With regard to the intervention dose and components of the study design, literature findings indicate that interventions averaging 12.7 weeks in duration (ranging from 2 to 52 weeks) yield small but significant increases in PA [32] and that daily text messaging has been associated with increases in PA [99]. However, in the systematic review and meta-analysis citing the duration and effectiveness of web- and text-based interventions, the overwhelming majority of studies were with White non-Latino adults [32]. The Hombres Salduables intervention will provide preliminary effect sizes of a 6 month web- and text-based intervention for diverse Latino men that uses less frequent text messaging than the daily text messaging identified in the PA literature [32,99]. Our findings, if supported via additional research, could help inform the study design for future interventions that involve text messages, including (and perhaps beyond) PA interventions targeted to diverse Latino men.

In addition, achieving the study aims will provide evidence for potential mediators and moderators of PA, which remain underexamined in Latino men. The mediators in this study are based on theoretical constructs (eg, self-efficacy and social support) associated with increases in PA among Latina women and other racial or ethnic subgroups [11-15,28,77]. Although, well-established evidence points to the effects of these mediators on PA, this study provides preliminary evidence as to whether these mediators explain changes in PA among diverse Latino men.

Although the intervention focuses mostly on changing the psychological, behavioral, and economic barriers to PA, we will explore potential moderating effects of individual and environmental factors on PA. At the individual level, we will examine whether important demographics (eg, age, country of origin, marital status, and education), acculturation, or baseline stage of change (based on TTM) impact changes in PA among Latino men. At the neighborhood level, we will explore walkability and social conditions, which have not been reported in PA intervention studies with Latino men. Although many studies explore associations of neighborhood walkability with PA (including studies with Latinos) or as a potential moderator of intervention efficacy [100-104], associations between other neighborhood social conditions and PA remain unanswered. This study will provide preliminary evidence for some of these unanswered questions. For example, this intervention will examine whether perceived neighborhood-based police profiling impacts PA among Latino men. In previous qualitative studies with disparity groups, neighborhood race and gender-based police profiling is cited as a potential barrier to PA for racial or ethnic minority men [89,105]. Consequently, this study seeks to build upon the limited available evidence for Latino men by exploring the potential moderating effects of these individual and environmental variables in a PA-focused pilot RCT.

### Study Limitations and Strengths

Although the strengths of this study are numerous, a few potential challenges exist. Recruitment and retention of Latinos in PA interventions are often challenging [106], and it is possible that there are unforeseen confounding factors that may impact the study results. However, the purpose of this pilot RCT is to determine the feasibility, acceptability, and preliminary efficacy of the intervention. Although contamination is often a concern when implementing interventions, we do not expect this to be a significant problem. If members of the same family participated, they were yoked together. In addition, the PA Facebook group membership was accessible only to participants in the PA intervention, and the web- and text message–based components were tailored to each participant. Despite these potential limitations, the Hombres Saludables study aims to increase PA among diverse Latino men by engaging them in a culturally appropriate, low-cost, and easily accessible internet and cell phone–based intervention. The intervention also provided economic incentives, including a gym membership, to overcome the cost barriers associated with PA. To our knowledge, no studies have included all the combined intervention components that are incorporated into the Hombres Saludables study. We expect that this study will demonstrate preliminary efficacy and lead us to implement a larger RCT in the future. This intervention has the potential to be scalable and to reach and engage a large number of diverse Latino men, a disparity group with respect to PA and related chronic diseases and mental health [1,2,8-10,18].

## Appendix

Multimedia Appendix 1 Screenshots of the Hombres Saludables website.

Multimedia Appendix 2 Peer review of study grant proposal.

## Abbreviations

ANC: Active Neighborhood Checklist
MVPA: moderate-to-vigorous physical activity
PA: physical activity
PAR: physical activity recall
RCT: randomized controlled trial
SCT: social cognitive theory
S-TOFHLA: Short Test of Functional Health Literacy in Adults
TTM: transtheoretical model
